### Sample size

A power calculation (using an α(two-tailed) of 0.05, an anticipated effect size of 1.0 and a desired power of 0.8) suggested that a minimum number of 17 individuals per group
[47], thus a minimum N of 51 is required. This was based on the findings of Ljotsson *et al*.
[19], who reported a reduction in Global EDE-Q scores during self-help treatment of 1.1 (*SD* = 0.9). Notable variability in effect sizes for GSH treatment has been reported, with a recent systematic review of self-help interventions finding an overall effect size of 0.54 (95% CIs 0.36 to 0.72) across eight studies
[33] and another
[48] citing effect sizes for the frequency of binge eating ranging from .03 to 2.68. Effect sizes in such studies have been shown to be affected by factors such as level of pathology, sample (for example, community vs. clinical), and length of follow-up
[33]. Therefore, we are aiming for a minimum N of 51, but ideally closer to 44 per group
[47] to account for this variability and to minimise the risk of the study being under-powered. Thus, a minimum overall recruitment sample of 102 is sought, estimating dropout at 50%, slightly less than the 55% reported by Loeb *et al*.
[3] and higher than the approximately 23 % reported by Ljotsson *et al*.
[19]. Attrition rate has been considered as an important factor in evaluating such trials
[48]. Therefore, in the current study, an attempt is made to more clearly define individuals who do not complete treatment, for example, noting at what point participants ceased treatment (for example,
[49]).

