### Primary and secondary outcomes

The primary outcome will be frequency of objective bulimic episodes, as assessed by the Eating Disorder Examination Questionnaire (EDE-Q) (see below). Comparisons will be made between pre-treatment, post-treatment and follow-up in the intervention groups. Secondary outcome measures include overall eating psychopathology, other ED behaviours, such as self-induced vomiting, psychological distress, self-esteem, functional impairment and healthcare usage, assessed by self-report (see below). Some of these variables (for example, severity of ED psychopathology) will be considered as predictors of outcome, as well as considered aspossible mediating or moderating variables, such as therapeutic alliance or type of therapeutic support.

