### Statistical methods

Regarding the primary aim - comparing active treatment and control condition - results will be analysed using analysis of variance and *t*-tests. Effect sizes will also be assessed, and expressed appropriately (for example, Cohen’s *d*). Logistic regression analyses will look at predictors of outcome, and potential mediators and moderators might also be considered. However, a number of existing studies addressing this issue have been underpowered
[33] so this remains an important consideration. Differences in outcome variables will be analysed (for example, through χ^2^, regression) to examine attrition/drop-out. In terms of cost-effectiveness, analyses will be conducted based on data obtained through the health utilisation questionnaire, therapist time questionnaire and measures of functional impairment (CIA) and ED symptoms (EDE-Q).

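### The effect size of 1.0 behind 17 per group comes from a change in Global EDE-Q during treatment, so the 80% power is unsupported for active treatment versus waiting list on binge frequency

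*Protocol article*

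**What the plan says.** The Sample size section sets the design values as "using an α(two-tailed) of 0.05, an anticipated effect size of 1.0 and a desired power of 0.8" and derives "a minimum number of 17 individuals per group", which is 51 in total. It gives the basis as an earlier email-supported self-help trial, "who reported a reduction in Global EDE-Q scores during self-help treatment of 1.1", with SD 0.9.

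Other sections define the outcome and the comparison:
- Primary and secondary outcomes: "The primary outcome will be frequency of objective bulimic episodes". The next outcomes sentence puts the global construct in second place: "Secondary outcome measures include overall eating psychopathology".
- Statistical methods: "Regarding the primary aim - comparing active treatment and control condition - results will be analysed using analysis of variance and" t-tests.
- Objectives and hypotheses: both treatments are expected to beat the waiting list on the primary outcome and to be comparable with each other.

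The Sample size section also reports a systematic review of self-help "finding an overall effect size of 0.54 (95% CIs 0.36 to 0.72) across eight studies" and a second review with binge-frequency effects from .03 to 2.68. It would prefer about 44 per group. The recruitment minimum stays at 102 with 50% dropout assumed. The Abstract repeats 17 per group and 51 in total without qualification.

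**The concern.** A power statement is only as good as the effect put into it, and here the effect differs from the planned primary test in two respects.

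1. **Outcome.** The effect is on a global questionnaire score. The primary outcome is a frequency of episodes, and a standardised effect on one does not carry over to the other.
2. **Contrast.** The effect is described as a change during treatment. The primary aim compares randomised groups, so any improvement on the waiting list has to be subtracted.

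The comparison of email with face-to-face raises a further point. The treatments are expected to be comparable, so an effect of 1.0 is not the difference hypothesised there.

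What is at stake is how the results are read. A non-significant difference from the waiting list, or between the two treatments, could be taken as coming from a trial with 80% power for that question. The article does not show this.

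**Working it through.** **Inputs from the Sample size section:** two-sided α = 0.05; power 0.80; d = 1.0; change 1.1 with SD 0.9; review effect 0.54 (0.36 to 0.72); preferred size 44 per group; 50% dropout.

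**1. The plan's figure.** The normal approximation is n = 2(1.960 + 0.842)²/d² = 15.7 at d = 1.0, so 16 per group. The exact noncentral-t calculation for two independent groups gives 16.7, so 17, with power 0.807 at 17. The total is 3 × 17 = 51, and 51/(1 − 0.50) = 102. All the stated figures reproduce.

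**2. Which test the 17 belongs to.** The other calculations tried do not give 17:
- paired t-test at d = 1.0: 9.9, so 10
- paired t-test at 1.1/0.9 = 1.22: 7.4, so 8
- independent t-test at 1.22: 11.6, so 12
- one-sided independent t-test at d = 1.0: 13.1, so 14

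The 17 is therefore a between-group figure, while the effect cited for it is worded as a change during treatment.

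**3. What d = 1.0 would require on Global EDE-Q.** Assume that 0.9 is the SD of change in both arms (the article does not say) and that the waiting list improves by w points. Then d = (1.1 − w)/0.9.
- w = 0: d = 1.22, 12 per group
- w = 0.2: d = 1.00, 17 per group
- w = 0.5: d = 0.67, 37 per group

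**4. Sensitivity to the section's own review effect** (independent t-test, two-sided 0.05):

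| True d | Power, 17 per group | Power, 44 per group | n per group for 80% |
|---|---|---|---|
| 0.36 | 0.17 | 0.39 | 123 |
| 0.54 | 0.33 | 0.71 | 55 |
| 0.72 | 0.53 | 0.92 | 32 |
| 1.00 | 0.81 | >0.99 | 17 |

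The smallest effect detectable with 80% power is d = 0.99 at 17 per group and d = 0.60 at 44 per group. The assumed 1.0 lies above the upper limit of the quoted interval, 0.72. Over the binge-frequency range, power at 17 per group runs from 5% (d = 0.03) to above 99% (d = 2.68), so that range settles nothing.

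**5. Email versus face-to-face.** The expected 95% CI half-width in SD units is t × √(2/n).
- 17 per arm: 2.037 × √(2/17) = 0.70
- About 25 per arm: 2.011 × √(2/25) = 0.57. This applies if all 17 waiting-list participants stay, are re-randomised 1:1 as the Allocation section allows, and are included (17 + 17/2 ≈ 25).

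**The case against.** The strongest reply has five parts.

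- **The arithmetic is correct.** This stands. A reader might infer that the 80% power applies to no planned comparison. That goes too far: 17 per group does give 80% power for active treatment versus waiting list if the true between-group difference is 1 SD.
- **The within-group reading rests on wording alone.** This stands too. The source is not at hand, the Background says that trial had a waiting-list control, and the article does not say what the 0.9 is the SD of. It also used 1.0 rather than 1.22, so some allowance for waiting-list improvement cannot be excluded. The outcome mismatch does not depend on this reading.
- **The 0.54 has no stated outcome or comparator.** This is correct, and the binge-frequency range of .03 to 2.68 includes 1.0. A reader might infer that the trial's real power is 33%. The documents do not support that; it is a scenario. It also counts 17 completers per group: if outcomes were obtained from all 34 recruited per arm, power at 0.54 would be 0.59.
- **The article admits the uncertainty.** It reports variable effects, prefers 44 per group to reduce the risk of low power, and plans a pilot to refine the size (Protocol adherence and untoward events). This softens the point without curing it. The recruitment minimum of 102 yields 51 completers, whereas 44 completers per group at the same dropout would need 132/0.50 = 264.
- **No power is claimed by name for email versus face-to-face.** This is true, and the Abstract gives no power figure at all. But the 17 is stated per group for all three arms, with no indication of which comparison it serves. An equivalence margin may be left to a fuller document, and its absence is not part of this point.

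**Conclusion.** The point holds in a limited form. The calculation is right, but d = 1.0 is justified by a secondary outcome and, as worded, by a change within treated patients. It is not supported for the primary comparison of active treatment with waiting list on frequency of objective bulimic episodes.

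No single corrected sample size follows, because the article gives no between-group effect on binge frequency with its SD. What can be shown is how far the claim depends on the input: power with 17 per group falls from 81% at d = 1.0 to 33% at d = 0.54, and lies between 17% and 53% across 0.36 to 0.72. These figures assume a two-sample t-test on a roughly normal outcome, with completers only. The disclosures about variability and the pilot do not change the stated minimum or its basis.

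**What to change.** Change the wording in two places.

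**Sample size section**
- State that 17 completers per group give 80% power only if the true standardised difference from the waiting list is about 1.0, and that this value is an assumption taken from another outcome and not an estimate for binge frequency.
- Add the sensitivity as a scenario: at d = 0.54, power is about 33% with 17 and 71% with 44 per group, with 17% to 53% at 17 per group over 0.36 to 0.72; 80% would need 55 per group.
- State that the 80% does not apply to email versus face-to-face. Give the expected 95% CI half-width instead: about 0.70 SD at 17 per arm, or about 0.57 SD at about 25 per arm if all re-randomised waiting-list participants are included.

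**Abstract**
- Qualify the minimum of 17 per group and 51 in total in the same way.

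The cost is a few sentences and no extra patients. The downside is that the stated power becomes less favourable.

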### Allocation

Participants who have given written consent to participate will be randomly assigned to a waiting list, face-to-face GSH, or email GSH condition, with a 1:1:1 allocation as per a computer-generated random number sequence. Numbers are stratified (for example, 0 to 0.333) and correspond to allocation to a treatment arm. If participants in the waiting list condition wish to remain in the trial, they will then be randomised to one of the two treatment conditions using the same method, but with a 1:1 allocation. In order to further enhance allocation concealment, the allocation for the first cohort of cases (the number is not disclosed here) has been determined *a priori*. If more individuals than this are recruited, the procedure will be repeated. Reviews have highlighted unclear randomisation procedures in many RCTs
[33], and this method should limit predictability of allocation due to use of “a random and unpredictable assignment sequence” (
[50]; see also
[51]). Although this was conducted by the Chief Investigator (CI) (rather than an external researcher), sequence generation was completed prior to the first participant being recruited and participants are allocated only after full informed consent is received. In line with GCP guidance, full consent is obtained at least 24 hours after meeting with a member of the research team, and thus treatment allocation is not known at the time of recruitment, keeping allocation concealed until treatment is assigned
[50].

### Data collection

Data from the EDE-Q provide the primary outcome variable - binge eating frequency. Secondary variables include compensatory behaviours (for example, self-induced vomiting), and ED psychopathology, as well as constructs assessed by the other measures (self-esteem, psychological distress, functional impairment). Weight and BMI are not outcome variables, but may be included in analyses, for example, to give demographic information or as covariates. Other routine demographic information (for example, ethnicity) will also be recorded. Participants are asked to complete self-report measures (mailed or otherwise given by hand) at start-of-treatment, end-of-treatment and six-month follow-up (with the exception of the HAq-II; see Table 
2). Data will be stored on a secure computer server and analysed with computer statistics software (for example, SPSS **IBM Corporation, Armonk, NY, USA**). Oxford is the lead site for data coordination. In order to promote data quality, data will be examined for impossible values and a sample of electronic data (around 10%) will be double-checked by another researcher with raw data. Blinding is not used in this study, and so an emphasis on appropriate outcome measurement and allocation concealment is crucial
[50,51].

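### The 10% data check treats the primary episode count like any other item; verifying that one item in full would be a cheap, minor improvement

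*Protocol article*

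**What the plan says.** The Primary and secondary outcomes section fixes the endpoint: "The primary outcome will be frequency of objective bulimic episodes", taken from the EDE-Q. The Data collection section describes how the forms arrive: "Participants are asked to complete self-report measures (mailed or otherwise given by hand) at start-of-treatment, end-of-treatment and six-month follow-up". The same section gives the quality check: "data will be examined for impossible values and a sample of electronic data (around 10%) will be double-checked by another researcher with raw data". The article does not set the primary item apart from the others, and it states no error rate or tolerance.

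The Sample size section plans "using an α(two-tailed) of 0.05, an anticipated effect size of 1.0 and a desired power of 0.8", which "suggested that a minimum number of 17 individuals per group". It adds that "a minimum overall recruitment sample of 102 is sought, estimating dropout at 50" per cent. The Allocation section randomises "with a 1:1:1 allocation as per a computer-generated random number sequence". The Statistical methods section compares the conditions by analysis of variance and t-tests.

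**The concern.** The primary outcome is a single number per form with a wide plausible range. An impossible-value check works well on an item bounded at 0 to 6, where a 7 stands out. It does little for an episode count: 4 keyed as 40 over a month is still possible. For slips of that kind the 10% comparison with raw data is the only safeguard the article states, and it leaves about nine in ten primary values uncompared.

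The planned groups are small and are compared by means. One large false count would move a group mean and widen its standard deviation. The stake is therefore some loss of precision on the primary comparison, in a trial where that item could be verified in full at very little cost.

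**Working it through.** **Inputs from the article.** About 10% of electronic data checked; 17 per group, 51 in total, 102 to be recruited at 50% dropout; 1:1:1 allocation; assessments at baseline, 12 weeks and six months; no six-month follow-up for the waiting-list period; waiting-list participants who stay are re-randomised 1:1 to the two treatments.

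**Inputs assumed.** Keying error rate of 0.1% to 2% per value; entry by hand from paper forms; a skewed count; a 10% sample drawn at random; re-randomised participants assessed at end of treatment and at six months, with their 12-week waiting-list form serving as their pre-treatment form.

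**1. The plan's own figures.** A two-sample t-test with two-sided α 0.05, d = 1.0 and power 0.8 needs 16.7, so 17 per group (power 0.807 at 17). Then 3 × 17 = 51 and 51 / (1 − 0.5) = 102. These reproduce, and the point does not touch them.

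**2. Number of primary values.** With 102 recruits there are 34 per arm.
- Nobody lost: 34 × 2 × 3 + 34 × 4 = 204 + 136 = 340.
- Half give baseline only: 34 × 2 × (1 + 2 × 0.5) + 34 × (1 + 3 × 0.5) = 136 + 85 = 221.

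A 10% check covers about 22 to 34 of these.

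**3. Chance of missing a slip.** One in-range error escapes with probability 1 − 0.10 = 0.90. All of k errors escape with probability about 0.9^k; for k = 3 this is 0.73.

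**4. Expected errors, and the chance that the sample shows none.** With error rate e, expected errors = 340e, of which 0.9 × 340e are not sampled. P(no error in the 34 sampled values) = (1 − e)^34.

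| Assumed e | Errors in 340 | Not sampled | P(sample shows none) |
|---|---|---|---|
| 0.1% | 0.3 | 0.3 | 0.97 |
| 0.5% | 1.7 | 1.5 | 0.84 |
| 1% | 3.4 | 3.1 | 0.71 |
| 2% | 6.8 | 6.1 | 0.50 |

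With 221 values and 22 checked, expected errors are 0.2, 1.1, 2.2 and 4.4, and (1 − e)^22 gives 0.98, 0.90, 0.80 and 0.64.

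**5. Size of one bad slip.** Entering 4 as 40 adds 36 episodes. It moves a 17-person mean by 36/17 = 2.1 and a 34-person mean by 36/34 = 1.1. If the SD is 10 to 20 episodes (assumed), 2.1 is about 0.1 to 0.2 SD.

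**6. Effect on the t-test, illustration only.** Simulated negative binomial counts, means 16 and 6, dispersion 1, 20,000 repetitions. Every error adds or drops a digit and no range check is applied, so the harm is overstated.

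| Per group | e | Power, no errors | Errors unchecked | 10% corrected |
|---|---|---|---|---|
| 17 | 0.5% | 0.681 | 0.653 | 0.657 |
| 17 | 2% | 0.678 | 0.583 | 0.588 |
| 34 | 0.5% | 0.957 | 0.920 | 0.924 |
| 34 | 2% | 0.956 | 0.822 | 0.831 |

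The mean difference moves little, from 10.0 to about 10.2 at 0.5% and 10.8 at 2%. Its standard deviation rises more: at 17 per group and 0.5%, from 4.3 to 5.1. The main effect is noise, and correcting 10% of the errors recovers little of the loss.

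**The case against.** The strongest reply is that nothing here is wrong. A range check plus independent comparison of a sample with raw data is a recognisable quality procedure. It conflicts with no other section and enters no stated figure. That stands, and it limits the point to a suggested improvement.

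A second reply is that a sample check can also estimate the error rate and trigger wider checking, and that such rules commonly sit in a full protocol or data-management plan. This also stands. A reader might infer from one sentence in an article that 90% of the final primary data will stay unverified whatever the sample shows. The article does not support that, and the point does not rest on the absence of an escalation rule.

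Third, a reader might infer that checking every value of every questionnaire would be trivial. It would not. The CORE-OM (34 items), RSES (10) and CIA (16) make 60 items, so 60 × 221 to 60 × 340 gives about 13,000 to 20,000 values. Only the single primary item is cheap to verify in full.

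Fourth, a reader might infer that damaging errors are probably present and will go unseen. That depends on an error rate the article does not give. At 0.1% fewer than one error is expected in the whole trial. At 51 end-of-treatment values, the chance that none is wrong is (1 − e)^51 = 0.95, 0.77 and 0.60 at 0.1%, 0.5% and 1%. Many errors would also be off by only an episode or two and hardly matter.

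What remains is that a plausible slip in the primary count escapes the stated check about nine times in ten, and that full checking of this one item costs little.

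**Conclusion.** The point holds as a minor, low-cost improvement. The stated check is poorly matched to the primary count: the search for impossible values does not reach in-range slips, and the 10% sample misses each with probability about 0.9. Among at most 340 primary values, between 0.3 and 6.8 errors are expected for assumed rates of 0.1% to 2%. At 0.5% the illustrative loss of power, with the 10% check applied, is about 2 to 3 points (0.681 to 0.657 and 0.957 to 0.924). At 2% it is about 9 to 13 points (0.678 to 0.588 and 0.956 to 0.831). The simulation exaggerates both.

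The size rests on assumptions the article does not settle: the error rate, manual entry from paper (inferred from forms being mailed or handed over and from the reference to raw data), and the skew and spread of the counts. The documents do not show that material errors will occur, nor that the treatment comparison would be seriously biased.

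**What to change.** Before analysis, have the second researcher who is already assigned to checking compare the objective-bulimic-episode item with the raw form for every participant at every time point. Keep the 10% sample for all other items, alongside the search for impossible values.

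This means about 220 to 340 single-number look-ups. At an assumed one minute each, 340 take about 5.7 hours. It needs no new staff and leaves the hypotheses, analysis and sample size unchanged. The only downside is the checking time.

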### Statistical methods

Regarding the primary aim - comparing active treatment and control condition - results will be analysed using analysis of variance and *t*-tests. Effect sizes will also be assessed, and expressed appropriately (for example, Cohen’s *d*). Logistic regression analyses will look at predictors of outcome, and potential mediators and moderators might also be considered. However, a number of existing studies addressing this issue have been underpowered
[33] so this remains an important consideration. Differences in outcome variables will be analysed (for example, through χ^2^, regression) to examine attrition/drop-out. In terms of cost-effectiveness, analyses will be conducted based on data obtained through the health utilisation questionnaire, therapist time questionnaire and measures of functional impairment (CIA) and ED symptoms (EDE-Q).

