### Objectives and hypotheses of the RCT

The overall aim of the trial is to evaluate whether therapist support within GSH can be as effective when delivered via email as when delivered face-to-face. In this paper, we detail the design and methods of the current trial, and clarify the four main aims of the study. Specifically, these are to: (1) compare the effectiveness of face-to-face versus email GSH during treatment and at follow-up; (2) determine relative attrition and drop-out across the two treatments; (3) look at predictors of outcome in GSH (see below); and (4) determine the relative cost-effectiveness of these two treatments. The study also employs a waiting list control condition. The current paper describes the protocol on which the clinical trial is based, in line with suggested guidance (for example,
[23]).

In terms of the primary outcome measure, it is expected that both treatment conditions will be superior to the waiting list control condition (for example,
[4,18]). Although there is a limited amount of evidence in eating disorders, it is hypothesised that both treatments (face-to-face and email GSH) will be comparable in terms of effectiveness (for example,
[24]) in reducing binge eating frequency (see also
[21]). It is expected that similar results will be found with secondary outcome measures, drop-out and cost-effectiveness, although these variables have not yet been studied in detail in this way.

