## Discussion

Binge eating and related disorders are serious health concerns that are associated with a number of psychosocial, physical and occupational impairments (for example,
[58]). However, despite this and the risk of developing further complications, many individuals with eating disorders do not seek treatment. The results of this trial have the potential to offer a more flexible approach to the treatment of binge eating disorders, one that is patient-centred and, possibly, more cost-effective than existing treatments. A further aim is to evaluate the possibility of providing supervision over the Internet for eating disorder interventions, an idea that has not received much empirical attention, although some studies have used online supervision forums as part of mental health treatment (for example,
[59]). As is also suggested in the recent review of Aardoom and colleagues
[60], future studies would benefit from investigating therapeutic alliance across face-to-face and Internet-delivered treatments. Although some limitations of the current design exist (for example, imperfect allocation concealment, lack of blinding, lack of a placebo control (see
[31]), it is hoped that the results of this methodology will produce high ecological and external validity, as this (clinical) sample is recruited through a typical UK healthcare service, and may be described as a ‘pragmatic RCT’
[51].

Although Internet-delivered interventions have promise and appear to be highly acceptable (
[60]; see also
[61]), there are many potential drawbacks. Some studies report negative feedback regarding email communication (for example,
[7,62]), and individuals may require additional commitment or motivation than a treatment requiring face-to-face attendance. Further, although computer literacy is increasing (that is, the “digital divide” is decreasing;
[63]), some individuals do not have access to the necessary materials that may be required for email therapy (for example,
[64,65]). As a number of authors have suggested, it may be the case that ‘e-therapy’ is appropriate for some, but not for others. It is hoped that the results of the current trial might go some way towards supporting therapeutic equivalence for the two treatments, and thus give patients more choice when accessing treatment.

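### The protocol's overall aim is email versus face-to-face, but its analysis section makes active versus control primary and gives no criterion for calling the two treatments comparable

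*Protocol article*

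**What the plan says.** **Aim.** Under Objectives and hypotheses, the overall aim is to "evaluate whether therapist support within GSH can be as effective when delivered via email as when delivered face-to-face". The first of four specific aims is to "compare the effectiveness of face-to-face versus email GSH during treatment and at follow-up". The waiting list is introduced after these aims.

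**Hypotheses.** The same section has two. Against control, "it is expected that both treatment conditions will be superior to the waiting list control condition". Between the active arms, "it is hypothesised that both treatments (face-to-face and email GSH) will be comparable in terms of effectiveness" in reducing binge eating frequency, which is the primary outcome.

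**Intended use.** The Discussion hopes that the results "might go some way towards supporting therapeutic equivalence for the two treatments".

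**Analysis.** The Statistical methods section opens: "Regarding the primary aim - comparing active treatment and control condition - results will be analysed using analysis of variance and" t-tests. It adds effect sizes such as Cohen's d. The article states no equivalence or non-inferiority margin, no test of that kind and no confidence-interval criterion.

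**Sample size.** That section uses two-tailed alpha 0.05, effect size 1.0 and power 0.8 to reach 17 per group (51 in total), with closer to 44 per group as the ideal. The effect size comes from a reduction in Global EDE-Q of 1.1 (SD 0.9) during self-help treatment in an earlier trial.

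**Allocation.** Waiting-list participants who stay in the trial are randomised again, 1:1, to the two active arms.

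**The concern.** Two sections name different primary questions, so a reader cannot tell which contrast decides the trial. The methods offered suit only one of them. A t-test or ANOVA of active treatment against waiting list fits the superiority hypothesis. For the comparability hypothesis, the null of the same tests is no difference. Failing to reject that null says little when intervals are wide, and nothing else in the protocol says what result would count as comparable.

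At stake is the conclusion that the overall aim exists to reach: whether email support can stand in for face-to-face support when services are planned.

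**Working it through.** **1. The protocol's own figure.** A two-sample t-test with d = 1.0, two-sided alpha 0.05 and power 0.80 needs 16.7 per group, rounded up to 17 (power at 17 is 80.7%). Then 3 × 17 = 51, and 51 / (1 − 0.50) = 102. The stated numbers reproduce as a superiority calculation. The effect size behind them is not an email versus face-to-face difference.

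**2. Arm sizes for email versus face-to-face.** The stated minimum is 17 and the stated ideal is 44. If all waiting-list participants are re-randomised and included, each active arm gains half a group: 17 + 17/2 ≈ 25 and 44 + 44/2 = 66. The article does not say whether they enter this comparison, so both cases are shown.

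**3. Formulas, in SD units.** No SD for binge frequency is given.
- 95% CI half-width = t(0.975, 2n − 2) × √(2/n). At n = 17: 2.037 × 0.343 = 0.70. At n = 44: 1.988 × 0.213 = 0.42.
- Chance of non-significance if email is 0.5 SD worse = 1 − power of the two-sided t-test, with noncentrality 0.5/√(2/n). This is 1.46 at n = 17 and 2.35 at n = 44.
- Chance of showing equivalence = probability that the 90% CI lies within ±0.5 SD when the true difference is zero (two one-sided t-tests, by simulation). The 0.5 SD margin is assumed, as the protocol gives none.

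| Per active arm | 95% CI half-width (SD) | Non-significant if 0.5 SD worse | Equivalence shown, margin 0.5 SD, no true difference |
|---|---|---|---|
| 17 | 0.70 | 71% | about 1% |
| 25 | 0.57 | 59% | about 10% |
| 44 | 0.42 | 36% | about 50% |
| 66 | 0.34 | 19% | about 77% |

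**4. Scale.** The Sample size section cites an overall self-help effect of 0.54 from a systematic review. At 17 or 25 per arm the half-width exceeds 0.54. Even an observed difference of zero would then leave a loss as large as that whole effect inside the interval.

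**5. What an equivalence design would need.** For 80% power with no true difference and one-sided 0.05 on each side, n per arm = 2 × ((1.645 + 1.282)/margin)². A margin of 0.3 SD gives 191, 0.5 SD gives 69, and 1.0 SD gives 18. Only a margin of about 1 SD, the whole assumed treatment effect, comes close to 17 per arm.

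**The case against.** **No decision rule is stated.** A reader might infer that the trial will treat a non-significant t-test as proof of equivalence. The article never says so. It ties ANOVA and t-tests to active versus control, where they are appropriate, and it promises effect sizes. This stands: the 71% and 36% describe what would follow from such a reading, not a rule in the plan.

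**The aim is softer than a claim of equivalence.** The overall aim is worded as an evaluation, not a demonstration, and the Discussion sentence is a hedged hope. The trial never calls itself an equivalence or non-inferiority trial. This softens the point but does not remove it, because comparability on binge frequency is a stated hypothesis.

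**A margin could sit in an unseen analysis plan.** True of the margin. An analysis plan would still leave the protocol naming two different primary questions, and would not turn a superiority sample size into one set for this comparison.

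**The arms may be larger than 17 or 44.** Re-randomisation may enlarge them, and the protocol also plans a pilot to refine the sample size. This stands, and is why a range is given. A reader might infer that an inconclusive result is likely at any planned size; at 44 per group or more that is not established.

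**Other outcomes.** A reader might extend the point to secondary outcomes, drop-out and cost-effectiveness. The documents do not support that. Similar results are only expected there, the attrition methods are chi-squared and regression, and no hypothesis test is named for cost-effectiveness.

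**Conclusion.** Wrong as written. The Objectives and the Statistical methods section disagree on the primary comparison. The named tests cannot support the hypothesised comparability, no other criterion is given, and the trial is sized for superiority at d = 1.0.

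The size of the problem depends on the arm sizes reached. It is severe at the stated minimum of 17, still material at 44, and smaller at 66 if all re-randomised participants count. The percentages rest on an assumed 0.5 SD deficit or margin and on a normally distributed outcome. The primary outcome is an episode frequency and probably skewed, so they are illustrative. The conflict between sections, and the lack of a criterion, do not depend on them.

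**What to change.** - Make the Objectives and Statistical methods sections name the same primary comparison.
- Test each treatment against waiting list at 12 weeks for superiority.
- Report email versus face-to-face on objective bulimic episodes as a difference or rate ratio with a confidence interval. Conclude that they are comparable only if the interval lies inside a margin fixed before outcome data are seen; otherwise report the result as inconclusive. Alternatively, drop the equivalence wording and report only the estimate with its interval.
- State that a non-significant t-test is not evidence of equivalence, and that the sample size was not set for this comparison.
- Say whether re-randomised waiting-list participants enter it.

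**Cost.** Wording in the protocol and analysis plan, and a justified margin. The downside is that at the 17-per-group minimum the email versus face-to-face result will probably be inconclusive. At 44 per group or more, that depends on the margin and on whether re-randomised participants are included.
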